# A multicenter study comparing the outcome of catheter ablation of atrial fibrillation between cryoballoon and radiofrequency ablation in patients with heart failure (CRABL‐HF): Study design

**DOI:** 10.1002/joa3.12322

**Published:** 2020-03-15

**Keywords:** AF, cryoballoon, RF ablation

## Abstract

**Background:**

Catheter ablation of atrial fibrillation (AF) is increasingly performed worldwide in patients with heart failure (HF). However, it has been recently emphasized that AF ablation in patients with HF is associated with increased risks of procedure‐related complications and mortality. There are little data about the differences in the efficacy and safety between cryoballoon (CB) and radiofrequency (RF) ablation of AF in patients with HF.

**Methods:**

The CRABL‐HF study is designed as a prospective, multicenter, open‐label, controlled, and randomized clinical trial comparing the efficacy and safety of AF ablation between CB and RF ablation in patients with HF (LVEF ≤40%) (UMIN Clinical Trials Registry UMIN000032433). The CRABL‐HF study will consist of 110 patients at multicenter in Japan. The patients will be registered and randomly assigned to either the CB ablation or RF ablation group with a 1:1 allocation. The primary endpoint of this study is the occurrence of atrial tachyarrhythmias (ATs) at 1 year with a blanking period of 90 days after ablation. Key secondary endpoints are the success rate of the pulmonary vein isolation, total procedural time, left atrial dwelling time, total fluoroscopy time, radiation exposure, complication rate, composite of all‐cause mortality or HF hospitalizations, cardiovascular events, change in left ventricular ejection fraction, and change in quality of life.

**Results:**

The results of this study are currently under investigation.

**Conclusion:**

The CRABL‐HF study is being conducted to compare the efficacy and safety of catheter ablation of AF between CB and RF ablation in patients with HF.

## INTRODUCTION

1

Atrial fibrillation (AF) often coexists with heart failure (HF) and the presence of AF in patients with HF is associated with increased risks of the hospitalizations, strokes, and mortality.^1^, ^2^ Electrical pulmonary vein isolation (PVI) by catheter ablation has been established as an essential treatment for AF since Haissaguerre et al first reported the presence of arrhythmogenic triggers in the muscular sleeves of pulmonary veins (PV).^3^ In patients with both HF and AF, catheter ablation has been shown to be superior to all other strategies such as medical therapy or cardiac implantable electronic devices plus an atrioventricular node ablation with significant improvements in the mortality, HF hospitalizations, left ventricular ejection fraction (LVEF), NYHA functional classification, 6 minute walk test, and quality of life (QoL).^4^, ^5^, ^6^, ^7^

The CASTLE‐AF study was a multicenter, randomized trial, which assessed the outcome of radiofrequency (RF) ablation of AF compared with medical therapy in patients with HF.^8^ The study proved that RF ablation of AF in patients with HF reduced the all‐cause mortality and HF hospitalizations as compared to medical therapy. Although the most widely adopted and established technique for AF ablation is RF ablation, which was also used in the CASTLE AF, the technical complexity of RF ablation generally demands a long learning curve and relatively long procedure time.^9^ Recently, the cryoballoon (CB; Arctic Front Advance; Medtronic) technology has emerged to simplify the PVI.^10^, ^11^ The FIRE and ICE study was a multicenter, randomized, noninferiority trial to compare the two different technologies, CB and RF ablation, in patients with paroxysmal AF. CB ablation is noninferiority to RF ablation with respect to the efficacy and safety.^12^ Furthermore, the total procedure time, left atrial (LA) dwelling time, and total fluoroscopy time were significantly shorter in CB ablation than RF ablation. It is noted that patients with a reduced LV contraction were excluded from the FIRE and ICE study.

Recently, AF ablation has been increasingly performed in patients with HF.^13^, ^14^ However, the underlying pathophysiology differs between patients with and without HF.^15^, ^16^ Further, the fundamental mechanism of catheter ablation differs between CB and RF ablation as well. There have been no randomized controlled trials addressing the differences in the clinical outcomes between CB and RF ablation for the treatment of AF in patients with HF. This study will aim to prospectively compare the efficacy and safety of catheter ablation of AF between CB and RF ablation in patients with HF.

## METHODS

2

### Aim

2.1

The aim of this study is to compare the efficacy and safety of catheter ablation of AF between CB and RF ablation in patients with HF.

### Study design

2.2

The CRABL‐HF study is designed as a prospective, multicenter, open‐label, controlled, and randomized, noninferiority clinical trial comparing the efficacy and safety of AF ablation at 1 year with a blanking period of 90 days after ablation between CB and RF ablation in patients with HF from 25 April 2018 to 31 March 2027 (Figure 1). The enrollment period is from 25 April 2018 to 31 March 2023. Eligible subjects will be randomly assigned to either the CB ablation or RF ablation group (allocation rate 1:1). The randomization will be stratified by the LA diameter. The study period will be extended if the number of enrollments is not be achieved during the period.

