#### Primary endpoint

2.7.1

The primary endpoint of this study is the occurrence of ATs at 1 year with a blanking period of 90 days after ablation.

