### Sample size

2.9

The estimated sample size is 110 (55 in each group). The sample size was calculated based on the primary hypothesis. The recurrence rate of ATs after an ablation of AF has been reported to be comparable between the CB and RF ablation in patients without HF, ranging 65%‐90%,^11^, ^12^, ^19^, ^20^ and the recurrence rate of ATs after CB ablation in patients with HF with an LVEF ≤40% has been reported to be equal to those without HF.^21^ Therefore, we hypothesized that the incidence of recurrent ATs after an ablation procedure could be 20% in the AF patients from previous studies in both the CB and RF ablation groups. The sample size for the randomized comparison was calculated as 51 patients per group with a power of 80% by a two‐sided 95% confidence interval for the difference in the population proportions with a width that is equal to 0.35 when the two estimated group sample proportions are equally 0.20. To cope with a potential loss‐to‐follow‐up, a minimum of 55 patients per group will be enrolled in the study. Withdrawn patients will not be replaced.

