### Statistical analysis

2.12

Comparisons between the randomized groups will be performed on the basis of the intention‐to‐treat (ITT) principle. A per‐protocol basis analysis will also be performed to assess the robustness of the conclusions derived from the ITT basis analysis. The Kaplan‐Meier method will be used to estimate the survival curve, and the log‐rank test will be used to compare the curves between the groups for the time‐to‐event variables. Categorical variables will be analyzed using a chi‐square test or Fisher's exact test. Continuous variables will be presented as the mean ± standard deviation or median with the interquartile range (25th‐75th percentiles) and compared with the Student's t test or Wilcoxon rank‐sum test, as appropriate. A *P* value < .05 will be considered significant. Up‐to‐date versions of JMP (SAS institute) will be used to conduct analyses. The patient demographic data and outcome of catheter ablation in each group will be collected descriptively as presented in Tables 1 and 2.

**Table 1 joa312322-tbl-0001:** Patient characteristics at baseline

Age, years, n (%)
Male sex, n (%)
Height, cm
Weight, kg
NYHA functional class
History of a heart failure hospitalization
Number of heart failure hospitalizations
Blood pressure, mm Hg
Heart rate, /min
Duration of atrial fibrillation, months
Congestive heart failure, n (%)
Hypertension, n (%)
Diabetes mellitus, n (%)
Stroke and/or transient ischemic attack, n (%)
Structural heart disease, n (%)
Coronary artery disease
Valvular heat disease
Dilated cardiomyopathy
Hypertrophic cardiomyopathy
Others
Postopen heart surgery
CHADS_2_ score
CHA_2_DS_2_‐VASc score
Echocardiographic data
Left ventricular ejection fraction, %
Left atrial dimension, mm (%)
Left atrial dimension, <50 mm
Left atrial dimension, ≥50 mm
Computed tomography data
Pulmonary vein diameter, mm
Cardiac implantable electronic device
Pacemaker
ICD
CRT‐P
CRT‐D
History of anti‐arrhythmic drug use, n (%)
Disopyramide, n (%)
Cibenzoline, n (%)
Aprindine, n (%)
Pilsicainide, n (%)
Flecainide, n (%)
Propafenone, n (%)
Bepridil, n (%)
Sotalol, n (%)
Amiodarone, n (%)
Verapamil, n (%)
Beta‐blocker, n (%)
Digitalis, n (%)
Others, n (%)
Laboratory data

**Table 2 joa312322-tbl-0002:** The ablation procedure and complications

Procedure time (groin puncture to catheter extraction), min
Left atrial dwelling time
Fluoroscopic time, min
For cryoablation
Total freezing cycles, n
Total freezing time, s

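### The article calls the trial noninferiority but states no margin and only tests of difference, so the analysis as published cannot establish noninferiority

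*Protocol article*

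**What the plan says.** **Design (section 2.2).** The trial is described as a "controlled, and randomized, noninferiority clinical trial comparing the efficacy and safety of AF ablation at 1 year", CB against RF ablation.

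**Primary endpoint (section 2.7.1).** The article states: "The primary endpoint of this study is the occurrence of ATs at 1 year with a blanking period of 90 days after ablation".

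**Sample size (section 2.9).** "The sample size was calculated based on the primary hypothesis", but that hypothesis is not written out. The figure of 51 per group is attributed to 80% power and to a "confidence interval for the difference in the population proportions with a width that is equal to 0.35". The interval is two-sided at the 95% level, and recurrence is taken as 20% in each group. The number is raised to 55 per group for loss to follow-up.

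**Analysis (section 2.12).** For time-to-event variables the log-rank "test will be used to compare the curves between the groups". Categorical variables get a chi-square or Fisher's exact test, and continuous variables a t or Wilcoxon test. The one decision rule is that P < .05 is significant. Comparisons are by intention to treat (ITT), with a per-protocol analysis as a robustness check.

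**The concern.** A noninferiority claim needs a margin, a reference arm, and a rule that a confidence limit must lie on the right side of that margin. The article names the design but gives none of the three. What it does give belongs to other kinds of trial: section 2.9 sets a precision target, and section 2.12 tests for a difference. The interval that determines the sample size does not reappear in the analysis.

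The conclusion on the primary endpoint is at stake. Under the stated rule the result is either a significant difference or no significant difference, and neither answers whether CB is acceptably close to RF. A margin chosen after the comparative data had been seen would not be credible.

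**Working it through.** **Inputs.** From section 2.9: expected recurrence 0.20 in each group, two-sided 95% interval of full width 0.35, 51 per group before and 55 after the allowance for loss, quoted power 80%. From section 2.12: significance at P < .05, taken here as two-sided. The margins and the alternative recurrence rates below are assumptions, because the article gives none.

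**Step 1. Reproduce the 51 per group.** For a continuity-corrected Wald interval on a difference of two proportions, both 0.20, the full width is

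W(n) = 2 × [1.96 × √(2 × 0.20 × 0.80 / n) + 1/n].

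- n = 51: 2 × [1.96 × 0.0792 + 0.0196] = 0.3497, which meets 0.35.
- n = 50: 0.3536, which does not.

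So 51 reproduces. Without the continuity correction the formula gives 41, as does the Newcombe interval. The formula that reproduces 51 has no margin and no power term.

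**Step 2. Could half the width be an unwritten margin?** Half of 0.35 is 0.175. With both true rates 0.20 and one-sided 0.025, noninferiority power is Φ(margin / √(0.32/n) − 1.96).

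- n = 51, margin 0.175: Φ(0.175/0.0792 − 1.96), about 60%.
- With the continuity correction of step 1: Φ((0.175 − 0.0196)/0.0792 − 1.96), about 50%.

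Neither is 80%, so 0.175 read as a margin does not account for the quoted power.

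**Step 3. Power at assumed margins.** Same formula, both rates 0.20, one-sided 0.025; √(0.32/55) = 0.0763.

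| Assumed margin | Power, 51 per group | Power, 55 per group | n per group for 80% |
|---|---|---|---|
| 0.10 | 24% | 26% | 252 |
| 0.15 | 47% | 50% | 112 |
| 0.175 | 60% | 63% | 83 |
| 0.20 | 71% | 75% | 63 |

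The margin that gives 80% power is (1.96 + 0.84) × √(0.32/n): about 0.222 with 51 per group and about 0.214 with 55. Both exceed the assumed recurrence rate of 0.20.

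**Step 4. What a non-significant test of difference would mean.** Exact binomial power of the uncorrected two-sided 5% chi-square test, 51 per arm, 20% recurrence in one arm:

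| Assumed true rate in the other arm | Power | Chance of missing it |
|---|---|---|
| 30% | 0.217 | 78% |
| 35% | 0.402 | 60% |
| 40% | 0.607 | 39% |

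Illustration: 10/51 against 18/51 is a difference of 8/51 = 15.7 percentage points, P = 0.076, Wald 95% interval −1.4 to +32.7 points. The result is not significant, yet it is compatible with an excess of nearly 33 points.

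**The case against.** The strongest reply is that this is a journal article. The full protocol and analysis plan are not shown, section 2.9 points to a primary hypothesis it does not spell out, and a margin may be written there. That limits the finding to the text as published. It does not remove it: the article gives its sample-size basis and its significance rule, and neither fits the declared design.

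The rates of 30%, 35% and 40% are not in the documents, and the power quoted for them is power to detect a difference, not noninferiority power. Both points are fair. The step 4 figures show only how little P > .05 would exclude; step 3 gives noninferiority power separately.

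Three stronger readings are tempting and should not be drawn:

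- **That P > .05 will be reported as noninferior.** No section says so. The article supplies no other route to a noninferiority conclusion, but that is a risk, not a stated intention.
- **That RF touch-up in the CB arm pulls the ITT comparison toward no difference.** Section 2.4.1 makes focal touch-up, with a cryo or an RF catheter, a specified step of the CB strategy when isolation fails. It is not crossover, a per-protocol set would not obviously exclude those patients, and no direction or size of bias is shown. A per-protocol analysis is planned in any case.
- **That the abstract contradicts section 2.2.** It calls the trial a "controlled, and randomized clinical trial comparing the efficacy and safety of AF ablation between CB and RF ablation" and omits the noninferiority label, but an abstract condenses and this carries no weight alone.

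**Conclusion.** The concern holds for the article as published. Section 2.2 declares a noninferiority trial, section 2.9 sizes it for precision, and section 2.12 analyses it for difference; the three must be reconciled. The stated analysis cannot establish noninferiority. The quoted 80% power belongs to no stated margin, and 55 per group reaches it only near 0.214.

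The mismatch itself is read directly from the text and depends on no assumption. The power figures depend on true rates of 0.20 in both groups, one-sided 0.025, a normal approximation and the assumed margins. The chances of missing a difference depend on 51 evaluable patients per arm and the assumed alternative rates. Whether an unpublished document contains a margin cannot be judged from here.

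**What to change.** Choose one course before any comparative data are reviewed, and make sections 2.2, 2.9 and 2.12 agree.

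**Preferred.** Remove the noninferiority label. Make the CB minus RF difference in 1-year atrial tachyarrhythmia recurrence, with its two-sided 95% confidence interval, the primary result. State that P > .05 will not be read as noninferiority or equivalence, and take out the 80% power statement. This matches how section 2.9 sized the trial. It costs only wording; the price is a weaker claim.

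**Alternative, if the full protocol already holds a justified margin.** State it as an absolute difference with RF as the reference arm. Conclude noninferiority only if the upper limit of the two-sided 95% interval for CB minus RF is below the margin in the ITT analysis, with the per-protocol result consistent. Restate the power that 110 patients give at that margin. This is not free: under the planning assumptions, any margin below about 0.214 leaves 55 per group short of 80% power, so the trial would need more patients or an openly stated lower power.

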**Figure 1 joa312322-fig-0001:**
[figure not shown]
Flow chart of the study. LVEF, left ventricular ejection fraction

### Patient eligibility and recruitment

2.3

Male and Female patients aged 20‐85 years with both HF and AF, and scheduled for catheter ablation of AF are eligible for the study. It is necessary for eligible subjects to be diagnoses with AF with at least one episode documented (≥30 seconds) and to have an LVEF ≤40%. Patients will be excluded if they have histories of previous catheter ablation and/or surgical procedure of AF before providing informed consent, or LA dimeter >55 mm (parasternal long‐axis view).

### Study procedures

2.4

#### The CB ablation

2.4.1

The detailed procedure has been described elsewhere.^11^ The fourth‐ or second‐generation CBs will be used in the CB ablation group. In brief, an atrial transseptal puncture will be performed using a standard Brockenbrough technique. The 28 mm CB will be introduced into the LA through a steerable sheath (FlexCath Advance, Medtronic) and be inflated proximal to each PV and pushed gently, aiming for complete sealing at the antral aspect of the PV. Contrast medium will be injected from the distal lumen of the CB to confirm the exact position of the inflated balloon in relation to the PV ostium. A 180 second freeze cycle will be performed at each PV.^11^ When the initial freezing fails to isolate the PV, the CB will be repositioned and a second freezing cycle will be applied. No further freezing cycle will be applied when PVI cannot be achieved after a maximum of five freezing cycles per vein. When the CB ablation cannot achieve the PVI, the steerable sheath (FlexCath Advance) will be exchanged to another sheath (SL0 or Agilis, Abbott) and additional focal ablation will be performed with Freezor Max (Medtronic) or RF catheter.

#### RF ablation

2.4.2

The detailed procedure has been described elsewhere.^17^ The three‐dimensional (3D) geometry of the LA and PVs will be depicted by a circular mapping catheter or PentaRay (Biosense Webster) by the use of a 3D mapping system; CARTO (Biosense Webster), NavX (Abbott), or Rhythmia (Boston Scientific). The ablation of the ipsilateral superior and inferior PVs will be jointly performed under navigation using the 3D mapping system. RF ablation will be performed with an irrigated 3.5 or 8 mm tip electrode catheter (Thermocool SmartTouch; Biosense Webster, TactiCath; Abbott, or Intella Tip MiFi; Boston Scientific). The RF ablation settings will be according to the center's standard of care, generally with a power of 30‐40 W, targeting an ablation index of 450‐550 for CARTO and lesion index of 4.0‐5.0 for NavX. The power and duration will usually be reduced to 20‐25 W for 20 seconds on the LA posterior wall near the esophagus.

### Follow‐up

2.5

Follow‐up will be conducted at 1 month, and then every 1‐3 months following the ablation procedure with clinic visits. Patients will be scheduled examinations, including 12‐lead ECGs, 24 hour Holter recordings (3, 12, 24, and 36 months after the procedure), and/or ambulatory electrogram recorder (HCG‐801, OMRON Healthcare Co., Ltd). In patients with cardiac implantable electronic device, home monitoring will be adapted to facilitate the continuous monitoring of AF episodes. In patients without cardiac implantable electronic device, one‐channel electrocardiograms will be recorded twice daily for 1 year after the procedure except for the blanking period of the 90 days with the use of ambulatory electrogram recorder. Echocardiography and QoL questionnaires will also be obtained during the follow‐up (3, 12, 24, and 36 months after the procedure). LVEF will be recommended to be calculated during sinus rhythm. The QoL will be assessed by AFEQT questionnaires.^18^ All documented atrial tachyarrhythmias (ATs) lasting ≥30 seconds occurring outside the blanking period of 90 days will be considered as a recurrence. In the case of recurrences outside the after ablation blanking period, it will be recommended to perform a second catheter ablation. The sum of the durations of all episodes of ATs regardless of lasting ≥30 seconds or not, will be calculated and expressed as a percentage with respect to 24 hours to assess the AF burden in patients with cardiac implantable electronic device.

Adverse events (AE) will be collected during the study periods. An AE is defined as any untoward medical occurrence in a subject in this study, regardless of whether the causal relationship of the AE with the ablation procedure.

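### Section 2.5 assigns rhythm monitoring by whether a patient has any implantable device, not by whether the device can detect atrial arrhythmia, so recurrence detection is weaker in a subset of unknown size

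*Protocol article*

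**What the plan says.** The primary endpoint (section 2.7.1) reads: "The primary endpoint of this study is the occurrence of ATs at 1 year with a blanking period of 90 days after ablation". Section 2.5 defines an event without regard to its source: "All documented atrial tachyarrhythmias (ATs) lasting ≥30 seconds occurring outside the blanking period of 90 days will be considered as a recurrence".

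Section 2.5 then describes how rhythm is observed:

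- All patients: "Follow‐up will be conducted at 1 month, and then every 1‐3 months following the ablation procedure with clinic visits", and "Patients will be scheduled examinations, including 12‐lead ECGs, 24 hour Holter recordings (3, 12, 24, and 36 months after the procedure), and/or ambulatory electrogram recorder".
- Patients with a device: "In patients with cardiac implantable electronic device, home monitoring will be adapted to facilitate the continuous monitoring of AF episodes".
- Patients without a device: "In patients without cardiac implantable electronic device, one‐channel electrocardiograms will be recorded twice daily for 1 year after the procedure", with the blanking period left out.

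The same section computes AF burden in device patients by summing the duration of all their AT episodes. Section 2.8 lists change in AF burden among the other variables.

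Table 1 (section 2.12) has the row "Cardiac implantable electronic device" with pacemaker, ICD, CRT-P and CRT-D beneath it, not divided by atrial sensing. The exclusion criteria (section 2.6.2) say nothing about device type.

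**The concern.** The branch is chosen by device ownership, whereas what matters for the endpoint is whether the device detects atrial arrhythmia. A device that senses only the ventricle does not record the atrial rhythm. In a population with LVEF ≤40% some patients may well carry one, and no eligibility rule keeps them out. Under the stated rule they fall in the home-monitoring branch, and the intensive alternative, the twice-daily recorder, is scheduled only for the other branch.

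Two things are at stake. First, low-burden paroxysmal recurrences in this subset are more likely to go undocumented and so to be counted as freedom from AT. That lowers the observed recurrence rate and, if it happens equally in both arms, shrinks any true difference. The trial is described as a noninferiority trial (section 2.2), so shrinkage leans towards the conclusion it hopes to reach. Second, an AF burden summed from a device that does not see the atrium is a false zero or a missing value.

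**Working it through.** **1. The plan's own figure.** Section 2.9 assumes 20% recurrence in both arms and a 95% confidence interval of width 0.35. With a continuity correction, the width at n = 51 is 2 × [1.96 × √(2 × 0.20 × 0.80 / 51) + 1/51] = 2 × (0.1553 + 0.0196) = 0.350, so the stated 51 per group is reproduced. Monitoring is not an input to this calculation, so no revised sample size follows from this point.

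**2. How much detection depends on the recorder.** From day 91 to day 365 the recorder schedule gives 2 × (365 − 90) = 550 strips. Visits every 1-3 months over about 9 months give 3 to 9 visits, taken as one ECG each. The 12-month Holter is counted once. For a patient with AT burden *b* (fraction of time in AT), episode length *e* hours and *n* spot ECGs:

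P(detected) = 1 − (1 − b)^n × (1 − b) × exp[−24b / (e(1 − b))]

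The values of *b*, *e* = 2 to 6 hours, and independence between strips are assumptions; none is in the document. Worked for b = 0.005:

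- With recorder (n = 559, e = 6): 0.995^559 = 0.061; Holter term 0.975; detection 1 − 0.059 = 0.94.
- Without (n = 3, e = 6): 1 − 0.985 × 0.975 = 0.04.
- Without (n = 9, e = 2): 1 − 0.956 × 0.937 = 0.10.

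| AT burden | Recorder, visits, 12-month Holter | Visits and 12-month Holter | Same, also counting the 3-month Holter as outside blanking |
|---|---|---|---|
| 0.5% | 94% | 4-10% | 6-16% |
| 1% | about 100% | 8-20% | 12-30% |
| 5% | about 100% | 34-68% | 49-84% |

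At 30% burden, visits and one Holter already detect about 96-100%. The loss is therefore confined to low-burden recurrence. ECGs prompted by symptoms and optional recorder use are left out; both would raise the columns without the scheduled recorder.

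**3. Effect on the primary endpoint.** Let *f* be the share of all patients whose device does not sense the atrium and *s* the share of their recurrences still found. Neither is in the document. Taking the plan's 20% as the rate seen under full monitoring, with the same underlying rate in the subset:

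Observed rate = 0.20 × [1 − f(1 − s)]

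| f | s = 0 (bound only) | s = 0.5 | s = 0.8 |
|---|---|---|---|
| 5% | 19.0% | 19.5% | 19.8% |
| 10% | 18.0% | 19.0% | 19.6% |
| 20% | 16.0% | 18.0% | 19.2% |
| 30% | 14.0% | 17.0% | 18.8% |

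**4. Effect on the comparison.** If *f* and *s* are equal in both arms, a true difference shrinks by the same factor, 1 − f(1 − s). As an illustration only, take 0.175, half the interval width in section 2.9:

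- f = 10%, s = 0: 0.175 × 0.90 = 0.158
- f = 20%, s = 0.5: 0.175 × 0.90 = 0.158
- f = 20%, s = 0: 0.175 × 0.80 = 0.140

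**The case against.** A reader might infer that these patients' recurrences are simply missed, or that the endpoint cannot be measured in them at all. The document does not support that. Section 2.5 schedules 12-lead ECGs and Holter for patients in general, its and/or wording leaves the recorder open to anyone, and any documented AT of at least 30 seconds counts. Eligibility is not limited to paroxysmal AF, and persistent recurrences would be found either way. The s = 0 column is therefore a bound and not an expectation.

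It can also be argued that home monitoring is given a purpose, continuous observation of AF, so it should be read as covering only devices able to do that, and that a condensed article leaves device specifications to the full protocol. The full protocol may indeed say more. But the published text is more than silent: it states a rule, and the rule schedules twice-daily recording by absence of a device. Permission to use the recorder is not a schedule, and discretionary use in an open-label trial is a weak substitute.

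Three further objections stand. The subset may be small. Device status is a baseline characteristic, so randomization spreads it over the arms on average; with 55 per group and no device factor in the allocation a chance imbalance can occur, but that is random error and not systematic bias. AF burden is neither the primary nor a key secondary endpoint. Leaving the Table 1 device rows undivided is not in itself an error.

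**Conclusion.** The point holds in limited form. The monitoring rule in section 2.5 uses the wrong criterion, and followed literally it gives patients whose device does not sense the atrium weaker AT detection than either intended branch, and no valid AF burden. The consequence is reduced detection of brief or asymptomatic recurrences.

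The size is uncertain and probably modest: an assumed 20% rate observed as about 18.0-19.6% if 10% of patients are affected, or about 16.0-19.2% if 20% are, for *s* between 0 and 0.8. The direction is towards no difference, which matters more for noninferiority than for superiority. These figures rest on an unknown device mix, unknown residual detection and equal misclassification in both arms. The document does not state that such devices will be enrolled, or how many. It is worth correcting because the remedy is cheap.

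**What to change.** In section 2.5, define the branches by capability: *patients without a device that detects and stores atrial arrhythmia episodes will record one-channel ECGs twice daily*, over the period already specified. Restrict the AF-burden calculation in section 2.5, and the matching variable in section 2.8, to patients with a capable device.

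Add one CRF item, atrial sensing yes or no, for every device patient. For patients already followed, whose recordings cannot be recovered, this item shows how many were affected in each arm and allows a sensitivity analysis of the primary comparison without them.

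The cost is a reworded sentence and one data item. The recorder is already in use in the trial. The small downsides are twice-daily recording for a minority of device patients and a smaller AF-burden subset.
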